# The fact and the contents, if there is an economic burden or reward for the study participants

There is a possible disadvantage regarding participation of the examinations, i.e. a temporal restriction of participating in the examinations and an economical burden by using public transportation.

- Since GBE/MST, GBE, and placebo are provided from Ohki Pharmaceutical Company without compensation, study participants have no cost allocation.
- Expense of MRI and neuropsychiatric examinations is beared by the company.

Reward of 10,000 yen will be paid to the participants who completed all examinations (at registration and at 24 weeks). If a participant may stop the study, partial reward may be paid.

# Assessment of adverse events

# Obtaining information

1. Investigators etc. must deal with any critical adverse events or incidences, and report them to a principal investigator.
2. A principal investigator must confirm items below to investigators.

**Confirmation items to investigators etc.**

| - 1. Name of adverse event / incidence   2. Classification of severity^1)^   3. Seriousness^2)^, reason   4. Predictivity (unknown, known)^3)^   5. Relation to intervention (medicine / medical apparatus)   6. Details of the effect / incidence (date, history, outcome, etc.)   7. Personal information of the participant (initial, age, sex) |
| --- |

**^1)^ Classification of severity**

For evaluation of adverse event / incident, Japanese version of NCI-CommonTerminology Criteria for Adverse Events v4.0 (CTCAE v4.0-JCOG) is used.

About the CTCAE v4.0-JCOG items of which grade is defined as an institutional standard, “JCOG reference range” will be adopted instead of each institutional standard. Precise information about “JCOG reference range” is available in the website (http://www.jcog.jp/doctor/tool/kijun.html）.

If there is no applicable grade in the NCI CTCAE grade, decision will be performed following the **Severity classification standard for adverse events**.

| **NCI CTCAE Grade** | **Severity classification standard for adverse events** |
| --- | --- |
| **Grade1** | No or mild symptom. Only clinical or laboratorical abnormality.  No needs to treat. |
| **Grade2** | Minimal/partial/non-invasive treatment.  Restriction of instrumental ADL*, except for age-appropriate personal activity. |
| **Grade3）** | Severe or medically important, but not critical.  Need in-patient treatment or extension of hospitalization.  Incapacity / inoperability. Restriction of self care ADL**. |
| **Grade4** | Life-threatening. Need emergency treatment. |
| **Grade5** | Death caused by the adverse event. |

* instrumental ADL

：preparation for meal, daily shopping, telephone use, management of money, etc.

** self care ADL

：bathing, changing, eating, toileting, and ingestion. Not bedridden.

**^2)^ Definition of seriousness**

| ① to be fatal  ② life-threatening  ③ to need in-patient treatment or extension of hospitalization   1. to be a permanent or salient disability / incapacity 2. inducing congenital abnormality in offsprings |
| --- |

Excluding events: hospitalization appointed by the study procedure, hospitalization for a therapy or an examination scheduled prior to the study registration, and hospitalization except for a treatment / examination of adverse events.

**^3)^ Definition of predictivity**

| **○ Unpredictable (Unknown)**  Those of which tendency of the expression number, frequency, and condition of a concerned event can not predict from the official documents (instruction sheet, reports, etc.) of the relevant medicine/appalatus.   - **Predictable (Known)**   Those of which tendency of the expression number, frequency, and condition of a concerned event can predict from the official documents (instruction sheet, reports, etc.) of the relevant medicine/appalatus. |
| --- |

# Description of adverse events

Investigators etc. must describe in the CRF about name, severity (seriousness, non-seriousness), reason of desiding seriousness, date of onset and prognosis, treatment, outcome (recovered, remission, recovered with sequera, not recovered, or death), relationship with the relevant medicine/appalatus, comments (causality and reason of decision) regarding all adverse events.

- 1. The name of adverse event must be written with diagnosis name/ disease name in the CRF. If diagnosis name/ disease name can not be specified or investigators etc. decide appropriate not to describe diagnosis name/ disease name, clinical condition or symptoms (including abnormal lab data) can be alternatively written in the CRF.
  2. Describe the treatments (yes/no) for adverse events of the participant.

③ Describe the outcome of adverse events.

| **Outcome** | **Description** |
| --- | --- |
| Recovered | The adverse event is eliminated, or it returns to original. |
| Remission | Although the adverse event is not completely recovered, it is almost eliminated or returns to almost original. |
| Recovered with sequera | Although the adverse event is returned to original, a sequera remains. |
| Not recovered | The adverse event is ongoing. |
| Death | The adverse event causes death. |

Definition of adverse events:

All undesirable or unexpected diseases and injury or symptoms (including lab data abnormality) regardless of causality to the study. Collection of adverse events will be performed from registration to the end or termination of observation of each participant.

# Response to the serious adverse event / incidents (including adverse events to be reported to head of the research institute)

# Response to the adverse event / incident

1. In case of the adverse events / incidents, investigators etc. must deal with them appropriately. Investigators etc. must investigate their cause with extreme care of the participant.
2. Investigators etc. must continue observation and check the outcome of symptoms and lab data abnormality until they are eliminated or return to original or are diagnosed normal as long as possible.
3. If the adverse event / incident is not recovered or irreversible at the end of the study, or if investigators etc. decide it is not necessary to chase, investigators etc. can cease the observation at the end of the study and describe the reason why it is decided as no-need to chase in the comment field of the CRF.

# Report to head of the research institute and principal investigator (research director)

1. Principal investigator of the research institute must report the serious adverse event / incident within a period described below. The report must use a format “**(No 9) Document regarding serious adverse events**”.
2. In case of multi-institutional joint research, principal investigator of the research institute must report the serious adverse event / incident within a period described below. The report must use a format “**(No 1) Document regarding serious adverse events**”.
3. If the other facility is the representative institute, response may follow a formula of the representative institute.

**Necessity and period of report to head of the research institute and principal investigator (research director)**

**Causality no**

**Causality yes**

|  | **Grade1/2/3** | | | **Grade4** | | **Grade5** | | **Others, medically important condition** |
| --- | --- | --- | --- | --- | --- | --- | --- | --- |
|  | **Predictable (Known)** | **Unpredictable (Unknown)** | | **Predictable (Known)** | **Unpredictable (Unknown)** | **Predictable (Known)** | **Unpredictable (Unknown)** |  |
|  | **hospitalization**  **yes／no** | **hospitalization**  **no** | **hospitalization**  **yes** |  |  |  |  |  |
|  | Reoprt  necessary | Reoprt  unnecessary | Initial report:  within 10d  Additional report: occasionaly | 1^st^ report: within 72h  2^nd^ report: within 7d  Additional report: occasionaly | | | |  |
|  | Reoprt  unnecessary | Reoprt  unnecessary | Initial report:  within 10d*  Additional report: occasionaly* | 1^st^ report: within 72h*  2^nd^ report: within 7d*  Additional report: occasionaly* | | | |  |

* during treatment or within 30 days from the last protocol treatment

# Report to joint research institution

1. In case of multi-institutional joint research, a principal investigator (research director) must report the fact described below to a principal investigator of the research institute where the adverse event / incident was occurred and of the joint research institutes, and request to report to head of the institute and ethical committee.

| - 1. A report of serious adverse event |
| --- |

1. A principal investigator of the research institute takes an action of a nessesary protocol following the head of research institute.

# In case of invasive study, describe the existence and contents of compensation for health damage caused by the research

If health damage is occurred on a participant by the research procedure, the institute and a principal investigator must take a nessesary action. Medical cost for the treatment of health damage will be paied from own health insurlance, and there is no financial compensation.

# When there is a possibility that important knowledge such as health of a research participant and genetic characteristics that can be passed down to descendants may be obtained with the implementation of the research, including incidental findings

There is a possibility of finding any critical diseases, such as brain tumore, brain absess, brain hemorrhage, brain infarction, brain artery aneurysm, arteriovenous malformation etc., by analysis of MRI data. Also, neuropsychological examination may occasionaly find cognitive decline.

Basically, these obtained data will not inform to participants. But, a participant can express his/her request about knowing information of any abnormality found in examinations on the form of informed consent. If a participant requested and if any of such abnormality will be found, an investigator will inform the participant about to ask a doctor.

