# Burdens, foreseeable risks (including possible adverse events) and benefits, comprehensive assessments of these subjects, and counterplan of minimizing burdens and risks

1. **Predicted benefits**

Study participants may get a partial health information, as the MRI findings will be checked by radiology specialists and the results will be provided.

1. **Foreseeable risks**

There are foreseeable risks and disadvantage regarding performed examinations, a temporal restriction of participating in the examinations, and an expected economical burden by using public transportation.

Risks and adverse events regarding blood sampling

Procedure of blood sampling will be the same as that performed in a health chek-up. Foreseeable events will be described below:

1. Bleeding from the site of puncture will be seen, and blueing may be expected. Counterplan is to perform complete astriction for 5min.

2. Tape eruption of skin may be occured because of a patch used on the site of puncture. Counterplan is to be asked if a participant had a risk of tape eruption. In that case, vinil tape will be used, instead of normal tape.

3. There is a possibility of allergic response by using alcohol rubbing cotton. Counterplan is to be asked about the existence of alcohol allergy. In that case, chlorhexidine swab will be used instead of alcohol swab.

4. There is a possibility of vasovagal reflex by pain or stress causing bad feeling and consciousness loss. Counterplan is to be asked as if a participant had a risk of vasovagal reflex before blood sampling. A participant may have a rest after blood sampling.

5. There is a possibility of the nerve injury along with blood sampling. The symptom of nerve injury is finger numbness and pain caused by injured peripheral nerves by needle puncture. The frequency is reported about 1/6000. Because it is anatomically difficult to completely prevent it, the blood sampling will be performed at an outpatient site following a recommended procedure as the ideal prevention. In case of the incident, a participant may consult a clinic using own medical insurance.

Risks and adverse events regarding MRI

1. The MRI apparatus may cause injury by iron materials existing in or on the body. Counterplans are described below:

・Ask several times about operation history, internal metals, and cardiac pacemaker, by means of document and interview.

・Confirm no metals on the body befor the examination.

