・Inform that the examination can stop anytime during the procedure if a participant will feel any abnormalities.

2. Since the MRI apparatus has strong magnetic field, metallic materials can be pulled and may physically injure a participant. Counterplans are described below:

・Metallic material without anchoring must not be stored in the MRI room.

・The exclusinve stuffs of MRI must control the procedures in the MRI room which has protective methods against expecting risks.

3. There is a possibility of finding any critical diseases, such as brain tumore, brain absess, brain hemorrhage, brain infarction, brain artery aneurysm, arteriovenous malformation, etc., by analysis of MRI. If any of such abnormality will be found, an investigator will inform the participant about to ask a doctor.

4. During MRI procedures, undesired noise, magnetic field, change of body temperature, and unconfortable position in narrow space may cause discomfort. As counterplan of discomfort, a participant can use a buzzer for alart any bad feeling. If a buzzer sounds, an operator must stop the procedure, and a doctor must check a participant’s condition. In case of difficultiness, the MRI procedure can be cancelled.

Risks and adverse events regarding GBE and GBE/MST

　GBE, sesame extract, and turmeric oil have been used as suppliments, and their safety has been established. No critical adverse event was reported. Digestive symptoms and thirsty have been reported as side effects. These symptoms will diminish after 3-4 days of cessation. If such side effects are strong, participation of this study can immediately be stopped.

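### The protocol has two conflicting rules on telling participants about MRI abnormalities: one section always discloses, another withholds unless the participant asked

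*Protocol*

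**What the plan says.** The Protocol deals with MRI findings in two sections.

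**Burdens, foreseeable risks and benefits.** Under predicted benefits, participants may gain some health information, "as the MRI findings will be checked by radiology specialists and the results will be provided". Under the MRI risks, item 3 lists serious brain diseases that a scan could reveal and continues: "If any of such abnormality will be found, an investigator will inform the participant about to ask a doctor". Neither statement depends on anything the participant has asked for.

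**Incidental findings** (the section on important knowledge that may be obtained about a participant's health). It opens with the same diseases: "There is a possibility of finding any critical diseases, such as brain tumore, brain absess, brain hemorrhage, brain infarction, brain artery aneurysm", followed by arteriovenous malformation. It adds that neuropsychological testing may reveal cognitive decline. The default follows: "Basically, these obtained data will not inform to participants". The exception is that "a participant can express his/her request about knowing information of any abnormality found in examinations on the form of informed consent". The action is then made conditional: "If a participant requested and if any of such abnormality will be found, an investigator will inform the participant about to ask a doctor".

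Item 16 of the matters to be covered in the informed consent document requires an explanation of how personal results, including incidental findings, are handled. It does not say which rule that explanation should give.

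**The concern.** The study team could hold a radiologist's report of a tumour, haemorrhage or aneurysm and find that the protocol tells them both to inform the participant and, by default, not to. Which happens would depend on the section that staff consult.

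Two things are at stake.

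- **Safety.** Scans are taken at baseline and at 24 weeks, so a lesion seen at baseline is known before or early in dosing. The Backgrounds section credits the flavonoids in the extract with reducing platelet aggregation, and the exclusion criteria bar people with a history of critical bleeding or on antithrombotic medication. No criterion names a baseline MRI finding; only the investigator's general discretion (item 15) would cover one. Under the incidental-findings section, a participant with a vascular lesion who had not opted in could take the capsules for 24 weeks without being told.
- **Honest description of benefit.** MRI results are the only predicted benefit listed. For anyone who does not opt in, the incidental-findings section takes that benefit away. A participant who believes that results come as a matter of course has little reason to make a separate request.

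**Working it through.** The protocol has no figure to reproduce on this point. The check is a comparison of the two sections, case by case.

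| Situation | Burdens, risks and benefits section | Incidental-findings section | Agree? |
|---|---|---|---|
| Listed abnormality found, participant made a request | Inform | Inform | Yes |
| Listed abnormality found, no request made | Inform | Do not inform | **No** |
| No abnormality found | Results provided (benefit statement) | No route to disclosure stated; the request covers abnormalities only | Unclear |

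The second row decides the matter.

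1. **Same event.** Both sections name tumour, abscess, haemorrhage, infarction, arterial aneurysm and arteriovenous malformation, and both refer to the analysis of the MRI. They do not govern different kinds of finding.
2. **Same action, different condition.** The two action sentences, "If any of such abnormality will be found, an investigator will inform the participant about to ask a doctor" and "If a participant requested and if any of such abnormality will be found, an investigator will inform the participant about to ask a doctor", are almost word for word the same. The second adds the participant's request as a condition, and the first has no such condition.
3. **Opposite defaults.** Without a request, the first sentence still requires disclosure. The second does not, and it follows the statement that data are in principle not passed on.
4. **No tie-breaker.** Neither section cites the other or is said to prevail. The incidental-findings section makes no exception for life-threatening or treatable findings. The consent-content list requires the topic to be explained but is neutral on the rule.

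**Number of scans covered.** Inputs: 159 participants (Sample size), MRI at baseline and at the endpoint (Methods, schedule), 20% dropout (Rationale for the sample size).

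- Upper bound, no dropout: 159 × 2 = 318 scans.
- If all of the planned dropout occurs before the second scan: 159 × 0.80 = 127.2, about 127 second scans, so 159 + 127 = 286 scans.

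These count scans to which both rules apply. They do not count people harmed. That number would be participants × probability of an abnormality × probability of no request, and the protocol gives neither probability.

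**The case against.** The best defence is that the sections can be read together. The MRI item is one line in a list of risks and countermeasures, while the incidental-findings section is the dedicated one. On that reading the specific section supplies the condition that the summary left out. Letting participants choose whether to learn of incidental findings can also be a deliberate and legitimate ethical decision. Every participant can opt in on the consent form, and if that form presents an explicit yes/no choice, few or none would fall under a silent default. The benefit sentence is itself hedged, since it opens by saying that participants may obtain partial information. Finally, a count of scans does not measure harm.

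Much of this is fair as a limit on the size of the problem. Withholding is a default and not absolute, the consent form is not available for review, and 318 is only an upper bound on scans covered. None of it removes the contradiction. That the dedicated section prevails is an inference, because the protocol states no precedence. The hedged benefit sentence still ends with an unqualified commitment to provide results, and the conflict between the two notification sentences stands without it. A clear consent form would help participants but would still leave staff with a protocol that instructs them both ways.

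**Conclusion.** The concern holds. The protocol gives opposite instructions for a participant with a listed brain abnormality who did not ask to be told, and nothing in it settles which applies. It also describes as a benefit something that another section withholds by default.

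The conflict covers all study scans, at most 318, or about 286 if the planned 20% dropout all precedes the second scan. The number of participants who would go uninformed is unknown. It requires an abnormality, no request, and staff following the incidental-findings section. The conclusion rests on the protocol text alone and assumes nothing about the consent form. It does not assert that disclosure on request is wrong as a policy, only that the protocol cannot hold both policies. The matter should be corrected because it bears on participant safety and the accuracy of consent. It does not affect the primary endpoint, sample size or analysis.

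**What to change.** Adopt one disclosure rule and state it identically in the predicted-benefits paragraph, item 3 of the MRI risks, the incidental-findings section and the consent form. The choice belongs to the investigators and the ethics committee.

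- **If abnormalities are always disclosed:** remove the non-disclosure default and the request condition from the incidental-findings section, at least for clinically important findings. State whether participants with normal scans also receive their results.
- **If disclosure stays on request:** add the request condition to item 3 of the MRI risks, and reword the predicted benefit to say that MRI results are given only to those who ask. State explicitly whether life-threatening or treatable findings are an exception. Put a clear yes/no choice on the consent form.

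The cost is an edit to the protocol and consent form, with ethics review of the change. By the protocol's own account radiology specialists already check the MRI findings, so no extra procedure is needed, and design, sample size and analysis stay as they are.

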# Potential use of samples and information for future research that is not identified at the time of consent / A possibility of providing it to other research institutions

The data obtained in this study are expected to be used in another or future researches approved by the Ethics Committee. Confirm and follow the intention at the time of participation in the research on whether or not the results can be diverted. If the research to be diverted has not already been approved by the Ethics Committee, apply again to the Ethics Committee.

# How to publish information about the study

# Registration of research outlines and results

A study responsibility person registers the outline of the research in the public database (UMIN), changes the research plan, and updates it appropriately according to the progress of the research.

Items, including human rights of participants, human rights of researchers etc., matters to be kept private for the protection of intellectual property, and matters approved by the head of a research institution after receiving the opinion of the Ethics Committee, shall be kept private, because it would significantly interfere with research from the viewpoint of protecting personal information.

